### Outcome measures

Data on clinical and economic outcomes will be collected from three main sources: self-report instruments, chart abstraction, and health plan administrative data (healthcare utilization and, where available, lab values) from participants’ employers. Because integrative medicine approaches treat the whole person, rather than simply targeting a specific disease or symptom, they can have broad impacts on health [25,29,35,36]. Therefore, a broad set of clinical and economic outcomes for the UAIHC will be captured (Table 1). These are each discussed below, starting with the self-report measures. All are collected at baseline (some directly and some as part of patients’ initial clinic intake form), and then 3, 6 and 12 months and semi-annually thereafter, unless otherwise noted.

### Self-report instruments – all patients

In addition to general socio-demographic data and an item on patients’ expectations of the clinic (both asked only at baseline), several factors are captured that could be seen as overall determinants of health and/or intermediate outcomes: diet, exercise, self-efficacy, stress, sleep and patient satisfaction. In addition, a number of specific (pain, fatigue, depression and anxiety) and global (quality of life, well-being, and work productivity) outcomes are captured. Each is described briefly below. It is estimated that it will take patients 15–20 minutes to complete these instruments.

• Diet quality. Diet quality is assessed by the Fruits and Vegetables module of the Behavioral Risk Factor Surveillance System [51]. Six items assess the type of fruits, vegetables, and legumes eaten in the past month and their frequency.

• Exercise & Physical Activity. Physical activity is assessed by the Exercise/Physical Activity module of the Behavioral Risk Factor Surveillance System [51]. Eight items assess the type, frequency, and duration of exercise/physical activity in the past month.

• Health self-efficacy. The Patient Activation Measure (PAM) is a 13-item self-assessment of an individual’s knowledge, skill, willingness, and confidence in managing their health and health care (activation) [52,53]. Scores stratify patients into four levels of health care activation.

• Stress. Several aspects of stress are captured. The Perceived Stress Scale (PSS) [54] is a brief measure that assesses the degree to which situations in one’s life are appraised as stressful in a global manner. Items tap how unpredictable, uncontrollable, and overloaded respondents find the stress in their lives to be. Two single items, found to strongly correlate with established multi-item measures, are used to tap the psychological response to stress and the amount of stress experienced in the past year [55].

• Sleep quality. Sleep quality is assessed by the 9-item Pittsburgh Sleep Quality Index (PSQI) [56]. The PSQI measures the quality and patterns of sleep over the past 1 month. It differentiates “poor” from “good” sleep by inquiring about seven areas: 1) subjective sleep quality, 2) sleep latency, 3) sleep duration, 4) habitual sleep efficiency, 5) sleep disturbances, 6) use of sleeping medication, and 7) daytime dysfunction.

• Patient satisfaction. The 2-item measure of patient satisfaction is from the Consumer Assessment of Healthcare Providers and Systems (CAHPS) Survey 2.0 Adult visit version [50,57]. These items are not included at baseline.

• Pain (global). Global rating of pain is assessed by a single-item pain visual analogue scale (*pVAS)*[58]. It measures severity of pain over the past week.

• Fatigue. Both a global rating and specific symptoms of fatigue are captured. Global rating of fatigue is assessed by a single-item fatigue visual analogue scale (*fVAS)*. It measures the severity of fatigue over the past week. The 9-item Fatigue Severity Scale (FSS) [59] assesses how fatigue affects motivation, exercise, physical functioning, carrying out duties, and interfering with work, family, or social life in the past 1 week.

• Depression. The 2-item ultra-brief Patient Health Questionnaire (PHQ-2) [60] is used to assess core symptoms of major depression. The items ask how often over the last 2 weeks participants were bothered by 1) having little interest or pleasure in doing things (anhedonia), and 2) feeling down, depressed, or hopeless (depressed mood). Scores of ≥ 3 have a sensitivity of 83 % and a specificity of 92 % for major depression. Patients with scores of ≥ 3 will also receive the full PHQ-9 (below).

• Generalized Anxiety Disorder. The 2-item ultra-brief Generalized Anxiety Disorder questionnaire (GAD-2) [61] is used to assess core symptoms of anxiety disorder. The items ask patients how often over the last 2 weeks they were bothered by 1) feeling nervous, anxious, or on edge and 2) not being able to stop or control worrying. Scores of ≥ 3 have a sensitivity of 86 % and a specificity of 83 % for Generalized Anxiety Disorder. Patients with scores of ≥ 3 will also receive the full GAD-7 below.

• Health-related Quality of Life. Health-related quality of life is assessed by the 12-Item Short Form Medical Outcomes Survey (SF-12) [62]. The SF-12 is a general measure of health status and well-being that assesses physical functioning, role limitations due to physical health, bodily pain, general health, energy/fatigue, social functioning, and role limitations due to emotional problems and mental health in the past 4 weeks.

• Psychological Well-being. Psychological well-being is assessed by the 5-item World Health Organization Well-Being Index (WHO-5) [63]. The WHO-5 assesses subjective quality of life as a dimension separate from social disability and asks about dimensions such as positive mood, vitality, and interest in life in the past 2 weeks.

• Health-related work productivity (absenteeism/presenteeism). Health-related work productivity is assessed by the 6-item Work Productivity and Activity Impairment questionnaire (WPAI) [64]. The WPAI is a self-administered instrument to assess the impact of disease on absenteeism (work time missed), presenteeism (reduced on-the-job effectiveness), and impairment in daily activity.

• Healthcare utilization. Four items based on Ritter et al. (2001) [65] ask about use of healthcare services in the prior period—from primary care providers outside of UAIHC, from specialists, from emergency rooms or urgent care centers, and overnight hospital stays.

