### Study design

A combination of observational quantitative and qualitative study designs will be used to measure the health and healthcare utilization outcomes of a primary care IM clinical model. Where possible, the clinical and economic impacts seen in this IM model will be compared to data available from one or more comparison groups (see discussion of comparison groups below). When comparison group data are not available for outcomes —e.g., for most of the self-report data and for the medical records data—baseline values for clinic participants will be compared to those measured during and after treatment. Table 1 shows the types of comparisons planned for each outcome data category for the observational study.

**Table 1 T1:** Outcomes measured for the UAIHC

	**Frequency of measurement**	**Pre/post comparisons**	**Comparisons against control group(s)**
Healthcare utilization and costs	One year prior and one year post-study enrollment	X	X^*^
Diet quality	BL, 3, 6, and 12 months	X	X^**^
Exercise	BL, 3, 6, and 12 months	X	X^**^
Patient satisfaction	3, 6, and 12 months	X	X^***^
Self-report health outcomes	BL, 3, 6, and 12 months	X	
• Self-efficacy			
• Stress			
• Sleep quality			
• Pain			
• Fatigue			
• Depression			
• Anxiety			
• Health-related quality of life			
• Well being			
• Work productivity			
• Condition-specific			
• outcomes			
Medical records data	3, 6, and 12 months	X	

BL = baseline (clinic enrollment).

^*^Primary outcome; comparison is to two matched control groups.

^**^Comparison here is to national (and where available statewide) averages from the Center for Disease Control and Prevention’s Behavioral Risk Factor Surveillance System (BRFSS) survey [51].

^***^Comparison here is to national and regional norms using the Consumer Assessment of Healthcare Providers and Systems (CAHPS) Adult Visit Survey 2.0 data [50].

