### Outcomes sample

Only patients who are members at UAIHC and who meet the inclusion/exclusion criteria are eligible to enroll in this study. Participation in the study will continue for at least one year after enrollment. It is anticipated that at least 500 patients will consent to participation during the first nine months of the study. Our primary outcome for our main analysis is change in total costs (see the Analysis section below). Using the standard deviation seen in a set of healthcare utilization data from a related group, a sample size of 200 patients should be sufficient to detect a small effect size (Cohen’s d = .20) difference in total costs at a .80 power using an alpha of .05. Therefore, our expected sample size of 500 may also allow for some subgroup analysis. Inclusion criteria: 1) Enrollment in primary care (members) at UAIHC; and, 2) adults ages 18 or older. Exclusion criteria: 1) currently pregnant at time of recruitment; 2) patients who attend the UAIHC clinic as “consultation-only” patients; and, 3) significant cognitive impairment to the extent that the individual is unable to understand the consent and respond to questionnaires.

All new patients will be advised by their primary care physician that they may be eligible to participate in a study to evaluate the effectiveness of the UAHIC. Prior to checkout, patients have an exit session with the University of Arizona (UA) Study Coordinator. During this session (or if necessary, through a follow-up phone call), the Study Coordinator will explain the nature of the study and make a determination of study eligibility, and if appropriate, consent the patient. Patients who joined the UAIHC before study start (July 2013) will also have the opportunity to participate. The study will be explained at their first UAIHC visit after study start.

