The fourth and fifth analyses will be the main outcome studies. The fourth study will be a prospective cohort study of the changes in outcomes from baseline to one year for all patients in the outcomes sample. The primary outcome for this analysis will be health-related quality of life measured in three ways (SF-6D [78], and the physical and mental component summary scores, all derived from the SF-12), with the other outcomes as secondary measures. The main comparison will be baseline to 12-month outcomes and the univariate analyses will use paired *t* tests for continuous data, and use the McNemar test for frequencies [79]. The data will also be examined for patterns of change over time in key outcomes, and the determinants of those patterns, using hierarchical linear modeling (HLM) techniques [80-82]. Fidelity measures with significant changes over time will be used as covariates [24] in these models, as well as other explanatory variables such as demographics, participants’ membership level and baseline diagnoses. If participant numbers for each of the five targeted condition allow, condition-specific outcomes will be examined for each. These same analyses will be applied to other secondary outcomes such as CVD event [70] and mortality [71] risk.

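### The past-year stress item is repeated at 3 and 6 months, when 75% and 50% of its recall window precede clinic entry, so its early values dilute and delay any real change

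*Protocol article*

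**What the plan says.** Under Self-report instruments – all patients, stress is measured by the Perceived Stress Scale and by two single items that "are used to tap the psychological response to stress and the amount of stress experienced in the past year". The article does not give the wording of the items, and the past-year period may belong to one of them or to both.

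The Outcome measures section sets the default schedule: measures are taken at baseline "and then 3, 6 and 12 months and semi-annually thereafter, unless otherwise noted". Table 1 lists stress under the row "Self-report health outcomes BL, 3, 6, and 12 months", and its footnote defines baseline as clinic enrollment. No exception is given for stress, although exceptions are given elsewhere. For patient satisfaction, for example, the article says: "These items are not included at baseline".

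For the fourth analysis, the Analysis section says: "The main comparison will be baseline to 12-month outcomes". It then adds: "The data will also be examined for patterns of change over time in key outcomes", using hierarchical linear models (HLM). The key outcomes are not listed.

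Table 1 marks no comparison group for stress, and the Comparison group(s) section makes each patient his or her own reference for such outcomes. The Study design section compares baseline with values both during and after treatment.

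**The concern.** A question about the last twelve months cannot separate time in the clinic from time before it when it is asked three or six months after entry. The other measures with a recall period stated as a length of time look back one week to one month, which fits inside the three-month gap between the early waves. The healthcare utilization items ask about the period since the previous one. Only the past-year item looks back further than the gap.

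Stress has no comparison group, so change within patients is the only evidence for it. If the 3- and 6-month answers are compared with baseline, or enter a model of change over time, the size and timing of the change will partly reflect the recall window. A prompt effect could be reported as small at first and then growing, and a short-lived one as lasting.

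**Working it through.** **Inputs.** The recall window is 12 months (Self-report instruments – all patients). The waves are 0, 3, 6 and 12 months (Table 1 and Outcome measures). Time zero is clinic entry (Table 1 footnote). The article gives no figure on this point to reproduce.

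**Step 1: share of the window before entry.** At month t the share is 1 − min(t, 12)/12.

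| Month asked | Months recalled | Before entry | Share before entry |
|---|---|---|---|
| 0 | −12 to 0 | 12 | 100% |
| 3 | −9 to 3 | 9 | 75% |
| 6 | −6 to 6 | 6 | 50% |
| 12 | 0 to 12 | 0 | 0% |

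**Step 2: what the item would show.** Assume that respondents average evenly over the year. The change from baseline is then the mean stress over (t − 12, t) minus the mean stress over (−12, 0). For an immediate, lasting change D this is D × t/12: 0.25D, 0.50D and D. Other courses, in units of the true change:

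| True course of stress | Month 3 | Month 6 | Month 12 |
|---|---|---|---|
| Falls by 1 at entry and stays down | −0.25 | −0.50 | −1.00 |
| Falls by 1 for the first 3 months only | −0.25 | −0.25 | −0.25 |
| Falls in a straight line to −1 at month 12 | −0.03 | −0.13 | −0.50 |
| Falls by 1 from month 6 | 0 | 0 | −0.50 |
| Flat throughout | 0 | 0 | 0 |
| 1 unit higher in the 3 months before entry, then back | 0 | 0 | −0.25 |

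The first row is a step that looks like a ramp. The second is a short benefit that looks lasting. The fifth shows that overlap alone produces no change. The sixth is a return to the earlier level at entry that stays invisible until month 12.

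**Step 3: the averaging assumption.** The documents do not say how respondents weigh the year. If they give weight w to the latest three months, a step change D shows as wD at month 3. Even weighting gives w = 3/12 = 0.25. A respondent who gives the recent months half the weight shows 0.50D, and one who thinks only of recent months shows D. The dilution is therefore smaller if recent months dominate, but the calendar shares in Step 1 do not change.

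**Step 4: patients already in the clinic.** The Outcomes sample section says: "Patients who joined the UAIHC before study start (July 2013) will also have the opportunity to participate". Suppose such a patient first answers k months after joining (k up to 12; the article gives no values). With even averaging, k/12 of the baseline window is already time in the clinic, and the baseline-to-12-month change is D × (1 − k/12). For an assumed k of 6 this is 0.50D.

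**The case against.** The strongest reply is that little depends on this item. The main comparison is baseline to 12 months, and for new patients those two windows do not overlap. The primary outcomes of the fourth analysis are the three scores from the SF-12, so stress is secondary. The key outcomes for the HLM are not listed, so nothing commits the team to modelling this item over time. The Perceived Stress Scale is on the same schedule. Table 1 also schedules stress as a whole, and the item-by-item forms may be in a fuller document.

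Most of this stands, and it keeps the point small. It does not remove it. The article states both the recall period and a schedule that applies unless an exception is noted, and it notes exceptions for other measures. The Study design section also plans comparisons of baseline with values during treatment, which would include months 3 and 6.

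A reader might go further and infer that the whole time pattern of this item is an artifact, or that the early waves cannot show an effect at all. The documents do not support that. With flat stress the item stays flat, and under even averaging a quarter of an immediate effect is visible at month 3 and half at month 6. The overlap misstates the size and timing of a real change but does not invent one.

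Two further arguments add little. At 18 months the window would share six months with the 12-month answer, but the planned cohort analysis ends at one year. Answers that share recalled months are correlated, but repeated measures are correlated anyway, and HLM allows for that. It does not correct the dilution.

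**Conclusion.** The recall period and the schedule do not fit each other, and the point holds as a minor one. For patients whose baseline is clinic entry, 75% of the window at month 3 and 50% at month 6 precede entry. Under even averaging, an immediate lasting change would appear at about a quarter and a half of its size at those waves and in full at month 12. The shares follow from the stated recall and schedule. The effect sizes rest on the averaging assumption and shrink towards no dilution if respondents think mainly of recent months.

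The baseline-to-12-month comparison is free of overlap for newly enrolled patients, although it compares two yearly averages rather than two points in time. For members who joined before July 2013, the baseline window may already include time in the clinic, so even that comparison may understate a change. No primary outcome or sample size is touched.

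**What to change.** Ask any past-year stress item only at baseline, at 12 months and yearly after that. If the questionnaires are already fixed, keep the item but analyse it only on that spacing. In either case, leave it out of the 3- and 6-month comparisons and of any HLM for change over time.

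Use the Perceived Stress Scale for the early waves, after confirming that its recall period is no longer than the three-month gap, since the article does not state it. Use the other single item at those waves only if its recall is not also the past year. For members who joined before July 2013, note in the analysis that their baseline window may include time in the clinic.

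The cost is having no early values for one secondary item. In return the questionnaire becomes slightly shorter, which helps with the patient burden that the Discussion lists as a limitation.

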### Data Collection

For the outcomes evaluation, data will be collected from patient charts and self-reports at four intervals—baseline (initial clinic visit), and at 3-, 6-, and 12-month follow up periods. Participants will receive a reminder email one week before each data collection due date. Baseline data will be due within one week of enrollment. In the email they will be directed to a secure website where they can access and complete the outcomes data collection instrument. If participants have not entered their data within 3 days of their due date, they will receive another reminder email, and those who have not entered their data within another 3 days of their due date will receive a call from the UA Study Coordinator. Healthcare utilization and cost data from healthcare claims will be obtained from their employer with study participant consent. These data will be collected for one year before and one year after clinic enrollment approximately 3 months after the 12-month follow up period to allow time for all incurred claims to be recorded. De-identified claims data for the comparison groups will be collected for the same period of time with “baseline” being defined by the average start date of study participants.

Because the intervention may change over time as clinic operations start up and mature [21], fidelity monitoring data will be collected monthly from study start for 6 months, then quarterly for 6 months, and then semi-annually. Patient-reported fidelity data will be gathered on a single randomly chosen day of the last week of the data collection month from all patients seen at the UAIHC clinic that day. This day will be selected by the UA research team using a simple computer generated randomization scheme and delivered to the UA Study Coordinator the week before the data collection week. A self-administered patient version of the “How is UAIHC doing?” questionnaire will be used for patients. For clinic personnel, fidelity data will be collected during the last week of each fidelity data collection month using an online self-administered practitioner and staff version of the “How is UAIHC doing?” questionnaire. Data from audits of randomly selected, de-identified patient charts and of administrative records will also be used to assess indicators of model implementation.

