### Self-report instruments – condition specific

For participants diagnosed by UAIHC with any of the identified study clinical conditions (low back pain, fibromyalgia, depression and anxiety), one or more of the following questionnaires will be added:

• Fibromyalgia Impact Questionnaire Revised - FIQR. The 21-item FIQR is a patient report of symptoms associated with fibromyalgia in three domains: physical functioning (9 items), overall impact (2 items), and symptoms (10 items) [66].

• Roland-Morris Disability Questionnaire – RMDQ. The RMDQ is a patient report of physical disability due to low back pain (Roland & Morris, 1983). The RMDQ contains 24 yes/no items focused on limitations in walking, bending over, sitting, lying down, dressing, sleeping, self-care, and daily activities.

• Patient Health Questionnaire 9 - PHQ-9. To assess clinical depression, the PHQ-9 [67,68] will be used with patients if the PHQ-2 screening score is ≥ 3.

• Generalized Anxiety Disorder 7 - GAD-7. When scores on the GAD-2 exceed the cut point of ≥ 3 on the New Patient Intake Form, the 7-item GAD-7 will be administered [69].

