### Data collected from medical records

These data will be collected at 3, 6, and 12 months. A medical records abstraction form will be used to collect the following from the patient chart for the period since the last outcomes data collection point. The results of any of the following lab tests will be captured: fasting glucose, lipid panel, thyroid stimulating hormone (TSH), glycosylated hemoglobin (HbA1c), inflammatory markers (erythrocyte sedimentation rate and high-sensitivity C-reactive protein), vitamin D status, and measures of anemia (hemoglobin, hematocrit, and mean corpuscular volume). Also captured will be each patient’s diagnosis(es), systolic and diastolic blood pressure, heart and respiratory rates, weight, waist circumference, body fat composition, smoking status, and whether the patient is on hypoglycemic, dyslipidemia, or hypertension medication. Composite scores (10-year cardiovascular disease (CVD) event risk [70], 10-year CVD mortality risk [71], and metabolic syndrome diagnosis [72]) will be captured from the chart when recorded, or will be calculated. Forced vital capacity and forced expiratory volume will be captured for participants with pulmonary disease.

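### Several planned pre/post comparisons rest on a baseline that is missing (satisfaction), stated in two ways (chart data) or dependent on an unclear trigger (PHQ-9, GAD-7)

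*Protocol article*

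**What the plan says.** **Analysis.** The fourth analysis takes baseline to 12 months as its main comparison, with paired t tests for continuous data and McNemar tests for frequencies. It applies the same methods to secondary outcomes, among them 10-year CVD event and mortality risk. The fifth analysis relates cost changes to changes in CVD risk.

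**Satisfaction.** Table 1 lists it at 3, 6 and 12 months and marks it for pre/post. The section on self-report instruments for all patients says of the two items: "These items are not included at baseline".

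**Chart data.** Table 1 lists 3, 6 and 12 months and marks pre/post. The section on data collected from medical records agrees on timing: "These data will be collected at 3, 6, and 12 months". It has each abstraction cover the time since the previous outcomes collection point. The Data Collection section says "data will be collected from patient charts and self-reports at four intervals", the first of them baseline. The Study design section names medical records data among the outcomes for which baseline serves as the comparator.

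**PHQ-9 and GAD-7.** The all-patients section says "Patients with scores of ≥ 3 will also receive the full PHQ-9 (below" and "Patients with scores of ≥ 3 will also receive the full GAD-7 below". The condition-specific section says the PHQ-9 "will be used with patients if the PHQ-2 screening score is ≥ 3", but for the GAD-7 it says "When scores on the GAD-2 exceed the cut point of ≥ 3 on the New Patient Intake Form, the 7-item GAD-7 will be administered". The lead-in to that section offers these questionnaires to participants with a clinic diagnosis of the condition. The Outcome measures section makes baseline, 3, 6 and 12 months the default schedule unless otherwise noted.

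**The concern.** A paired analysis needs both members of the pair, and the rule for collecting them must not depend on the outcome. A baseline that was never recorded cannot be recovered by a later analysis plan, so the collection rules have to be right in the protocol.

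At stake are a satisfaction change that cannot be computed, chart-derived changes (including CVD risk, which is used in both outcome analyses) whose baseline depends on which section the abstractor follows, and full-scale depression and anxiety changes whose direction of bias depends on an unstated choice of wave. All of these are secondary measures.

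**Working it through.** The document gives no figure for the share screening positive or for the number of full-scale pairs expected, so there is no stated figure to reproduce. Parts 1 and 2 are comparisons of text. Part 3 uses assumed inputs.

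**1. Satisfaction.** First measurement is at 3 months and the marked comparison is pre/post. Baseline-to-12-month pairs: zero. The comparison with CAHPS norms and a 3- versus 12-month change remain possible.

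**2. Chart data.**
- No baseline collection: Table 1; Data collected from medical records.
- Baseline collected or required: Data Collection (four intervals); Study design (baseline as comparator); Analysis (paired tests on CVD risk; change in CVD risk set against change in cost).
- The look-back of the 3-month abstraction may reach first-visit values, but the text does not say that they are recorded separately as baseline.

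Followed literally, the first pair of places yields no baseline record; the Data Collection section yields one. The places contradict each other.

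**3. PHQ-9 and GAD-7.** From the document: outcomes sample of 500. Assumed: 25% at or above the cut point at baseline, retest correlation r = 0.6, within-wave correlation of short and full scale c = 0.85, and the same true fall of 0.3 or 0.5 SD in everyone, on a bivariate-normal scale. Baseline positives: 0.25 × 500 = 125.

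*Reading A: screen re-applied at each wave.* A pair needs a positive screen at both waves. In simulation:

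| True fall | Baseline positives with a pair | Fall shown by pairs | Understatement |
|---|---|---|---|
| 0.3 SD | 32% (about 40 of 125) | 0.19 SD | 1 − 0.19/0.3 = 37% |
| 0.5 SD | 25% (about 31 of 125) | 0.32 SD | 1 − 0.32/0.5 = 36% |

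A wider grid used 10–30% positive and retest correlation 0.5–0.7, applied to the short scale as well as the full one:
- True fall 0.3 SD: pairs show 0.14–0.20 SD, an understatement of 33–53%.
- True fall 0.6 SD: pairs show 0.26–0.39 SD, an understatement of 35–57%; 13–34% of baseline positives keep a pair (about 7 to 51 patients).
- No true change: pairs show about zero, so this reading does not create a false benefit.

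*Reading B: screen at intake only, triggered patients followed.* All pairs are complete apart from dropout, but they are selected on a high baseline. Expected apparent fall = true fall + (1 − r) × c × λ, where λ is the mean of a standard normal above the cut point.
- 25% positive: λ = 0.318/0.25 = 1.27, so the regression term is 0.4 × 0.85 × 1.27 = 0.43 SD. True falls of 0.3 and 0.5 SD appear as 0.73 and 0.93 SD.
- 30% positive, r = 0.7: 0.3 × 0.85 × 1.16 = 0.30 SD with no true change.
- 10% positive, r = 0.5: 0.5 × 0.85 × 1.755 = 0.75 SD with no true change.

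The two readings err in opposite directions.

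**The case against.** A reader might infer that chart data have no baseline and that the CVD-risk baselines are lost. The document does not support that. The Data Collection section lists baseline for charts, the 3-month look-back starts from the initial visit, and the abstraction form is not shown. What stands is a contradiction between sections.

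A reader might also infer that the PHQ-9 and GAD-7 rule keeps only patients who did not improve. That fails twice. No section says the screen is re-applied at follow-up, and the condition-specific wording for the GAD-7 points to intake. Even if it were re-applied, it keeps patients still at or above 3, some of whom improved: the retained pairs above show a fall.

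Further, the PHQ-2 and GAD-2 are in the all-patients set on the default schedule, so the depression and anxiety rows of Table 1 can be paired for everyone. No sentence names a paired test on the PHQ-9 or GAD-7, and depression and anxiety are not among the five conditions marked for separate analysis. This limits the weight of part 3. It does not remove it, because Table 1 marks condition-specific outcomes for pre/post and these scales are listed among them.

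Following every baseline positive also has a cost. With a true fall of 0.3 to 0.5 SD it shows 0.73 to 0.93 SD, an error of about 0.43 SD, against 0.11 to 0.18 SD for re-applied screening. Complete pairs do not make an unbiased estimate of the clinic's effect. That objection stands and shapes the remedy.

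On satisfaction, the missing baseline is stated openly and the comparison actually described is with norms. The error is one table mark.

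**Conclusion.** The point holds as a set of inconsistencies to be reconciled. The satisfaction mark is certain, since no pair can exist. The chart schedule is a certain contradiction, and its consequence depends on which section is followed. For the PHQ-9 and GAD-7, the inconsistent trigger is certain and the size of the bias is conditional. Re-applied screening understates a true improvement by a little over a third under the central assumptions and by up to 57% across the grid. Intake-only screening adds 0.30 to 0.75 SD of apparent improvement. These figures rest on assumed screen-positive rates, correlations and a uniform shift, none of which the document gives. The SF-12 and total-cost primary outcomes are unaffected. The corrections are worth making, but the main conclusions do not depend on them.

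**What to change.** 1. **Satisfaction.** Remove the pre/post mark in Table 1. Keep the CAHPS norm comparison and, if wanted, add a 3- versus 12-month change under that name.
2. **Chart data.** Add baseline to Table 1 and to the medical records section so that both agree with Data Collection. Give the abstraction form a separate baseline field for values at or nearest before the first visit.
3. **PHQ-9 and GAD-7.** State one trigger and its wave, in the same words in both self-report sections, and reconcile it with the clinic-diagnosis lead-in. Repeat the full scale at later waves for everyone who received it at baseline. Name PHQ-2 and GAD-2 change in all patients as the main mood measure. Report full-scale change in screen-positive patients as descriptive, with a caveat on regression to the mean.

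The cost is one table edit, one more field on the abstraction form and a change to the survey branching. Screen-positive patients answer 7 to 9 extra items per wave, or 7 + 9 = 16 if positive on both. That burden matters somewhat, since the Discussion already names data collection burden as a possible cause of dropout. Repeating the full scale completes the pairs but does not remove regression to the mean, which is why the result should stay descriptive.
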